### Exclusion criteria

Participants will be excluded if they have a metal prosthesis in some part of the body, use a cardiac pacemaker, have either cognitive impairment, psychotic, or schizophrenic disorders as diagnosed by the rehabilitation team, neuropsychiatric co-morbidity, or use drugs that reduce either seizure threshold or spasticity. Individuals participating in intensive programs of rehabilitation that could bias the results will also be excluded.

EG before the rTMS procedure will identify possible brain bioelectrical abnormalities (such as interictal epileptiform discharge, generalized photosensitivity, burst suppression, hypsarrhythmia) that could be related to the possibility of epileptic discharges [30, 31], thus reducing the risk of seizures during rTMS, since the high-frequency stimulation might lead to cortical hyperactivity. If any of these abnormalities are identified, the individual will be excluded.

### Dropout criteria

Participants will be withdrawn from the study if they are not willing to continue their participation, cannot be present on the day of the experiment or miss a treatment section, and/or change their form of rehabilitation during the study.

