**Fig. 1 Fig1:**
[figure not shown]
*Flowchart* for the rTMS study protocol. The participants will be selected and the eligibility assessment will be applied. They will then be randomized and allocated to group 1 (starting with rTMS-active) or group 2 (starting with rTMS-sham). Five sessions of rTMS-active and sham will be applied to participants in each group over one week, with a washout period (two weeks). Assessments will be before and after each intervention period (i.e. sham and active) using the motor and sensory scales, spasticity scale, and surface electromyography

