### Intervention

All participants will attend the assigned rTMS intervention as follows: there will be ten sessions over two weeks, in which five sessions will be active and five will be sham, separated by a two-week washout period. The sessions will be administered consecutively and once a day. The researchers will be trained to perform both rTMS-sham and rTMS-active interventions.

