### Statistical analysis

#### Sample size

The sample size was calculated using statistical software (GPower 3.1.5) [57] on the main outcome measure (i.e. the motor score). This calculation was based on data from one study with a group of SCI individuals that received high-frequency rTMS at a frequency of 5 Hz on the vertex, which related to an improvement in clinical measures of the motor score [24]. The power was 0.80; the alpha was 0.05, the effect size was 0.65 (Cohen’s *d*). The sample estimation indicated that 14 participants would be necessary (i.e. seven per group). With an adjustment to allow for a dropout rate, we will recruit 20 participants.

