#### Data analysis

The analysis will follow a pre-specified analysis plan, based on comparing the groups as randomized (intention-to-treat). All data will be presented as mean ± standard deviation and summarized in frequency tables. We will use Microsoft Office Excel for Windows (version 2013) to store the data and the Statistical Package for Social Sciences (SPSS-IBM®) version 21 for Windows to perform statistical analysis. The normality and homogeneity of all variables (i.e. primary and secondary outcomes) will be tested with the Shapiro–Wilk and Levene’s test, respectively. For non-parametric data, the Friedman test will be used followed by the Wilcoxon post hoc test. We will use the ANOVA two-way (2 × 4) for the inferential statistic of the parametric data, with Tukey’s post hoc tests. Significance level will be set as α ≤ 0.05 and the effect size will be calculated by eta-squared (*ŋ*
^*2*^).

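### Withdrawing participants from the study for one missed session or a change of rehabilitation conflicts with the stated intention-to-treat comparison and would leave mainly completers in the planned tests

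*Protocol article*

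**What the plan says.** In the protocol article, *Dropout criteria* opens: "Participants will be withdrawn from the study if they are not willing to continue their participation". It then adds the participants who "cannot be present on the day of the experiment or miss a treatment section, and/or change their form of rehabilitation during the study" (section here evidently means session). The consequence in every case is withdrawal from the study. The section does not distinguish ending stimulation from ending follow-up.

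*Data analysis* describes an analysis "based on comparing the groups as randomized (intention-to-treat" and refers to a pre-specified plan that is not shown. It names the tests: "We will use the ANOVA two-way (2 × 4) for the inferential statistic of the parametric data", and "For non-parametric data, the Friedman test will be used followed by the Wilcoxon post hoc test".

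The exposure to the rule comes from *Intervention*: "there will be ten sessions over two weeks, in which five sessions will be active and five will be sham". The number of measurements comes from the Fig. 1 legend: "Assessments will be before and after each intervention period", which makes four per participant.

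*Sample size* arrives at 14 participants and continues: "With an adjustment to allow for a dropout rate, we will recruit 20 participants". It gives no dropout rate.

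**The concern.** Missing a session and changing rehabilitation both happen after randomisation, and both may depend on what the participant received. *Expected risks* mentions headache and muscle spasm during stimulation, so attendance could differ between active and sham weeks. *Expected benefits* anticipates motor gains, which might plausibly lead to a change of therapy. Group 1 receives active stimulation first and group 2 receives sham first, so early withdrawals could also differ by sequence.

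If participants are removed at these events and their later outcomes are never measured, the comparison is conditioned on adherence while carrying an intention-to-treat label. With 20 participants, each one lost also costs noticeable precision. In a crossover, a participant lost in the first period contributes no within-person contrast of active with sham.

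**Working it through.** **1. The two rules side by side.** Intention to treat, as *Data analysis* states it, keeps each participant in the randomised group regardless of adherence. That requires outcomes to be sought after non-adherence. *Dropout criteria* makes non-adherence a reason to leave the study. A participant who misses one session cannot both be withdrawn from the study and be followed to the last assessment.

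**2. What the named tests need.** There are 2 periods × 2 assessments = 4 measurements.
- The Friedman test uses only participants with all four.
- A standard repeated-measures ANOVA does the same.
- A Wilcoxon comparison needs both of the measurements being compared.

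If assessments stop at withdrawal, a participant withdrawn during period 1 has one of the four. A participant withdrawn during period 2 has three. Both fall out of the Friedman test and the standard ANOVA. The second also falls out of any Wilcoxon pair that involves the final assessment.

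**3. The plan's own figure.** Raising 14 to 20 implies an allowance w with 14 / (1 − w) = 20, so w = 1 − 14/20 = 0.30, or 6 of 20. This is back-calculated, not stated. The 14 itself (power 0.80, alpha 0.05, effect size 0.65) can be reached only under some readings, because the test, sidedness and correlation are not given. Nothing below depends on it.

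**4. How many the missed-session trigger alone could remove.** The article gives no miss rate, so p, the chance of missing any one session, is an assumption. It is taken as equal for all participants and independent between sessions. The share withdrawn over ten sessions is q = 1 − (1 − p)^10. The expected number is 20q. The chance that fewer than 14 remain is P(X ≥ 7) with X binomial(20, q).

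| p per session | q | expected of 20 | P(fewer than 14 remain) |
|---|---|---|---|
| 1% | 1 − 0.99^10 = 9.6% | 1.9 | 0.2% |
| 2% | 1 − 0.98^10 = 18.3% | 3.7 | 5.8% |
| 3% | 1 − 0.97^10 = 26.3% | 5.3 | 25.5% |
| 5% | 1 − 0.95^10 = 40.1% | 8.0 | 75.4% |

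The rate at which this trigger alone would use up the implied 30% is p = 1 − 0.70^(1/10) = 3.5%. That is a break-even value, not an estimate.

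**5. How many of these would have a complete first period.** The share withdrawn in period 1 is 1 − (1 − p)^5. At p = 1% this is 4.9%, leaving 9.6 − 4.9 = 4.7% withdrawn in period 2. At p = 5% it is 22.6%, leaving 40.1 − 22.6 = 17.5%. So a little under half of those withdrawn would already have both period 1 assessments.

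**6. Direction of the uncertainty.** If misses cluster in a few people, q is lower for the same average p. Absence on assessment days, changes of rehabilitation and refusals are not counted and would raise the loss.

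**The case against.** The strongest reply is that *Dropout criteria* says only who is withdrawn. It does not say that data already collected are discarded, that withdrawn participants leave the analysis set, or that only completers are analysed. They keep their randomised group, and the handling of missing data may be set out in the analysis plan that is not shown. This stands in part. A reader might infer that intention to treat becomes impossible, or that one missed session discards the whole participant. The article supports neither: an as-randomised analysis of the available data would still be possible. Nor does it say that its ANOVA is of the repeated-measures, complete-case kind, and the Friedman test is reserved for non-parametric data. The reply does not remove the conflict, however. The withdrawal rule governs conduct, and no analysis plan can recover outcomes that were never measured.

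A second reply concerns size, and it also stands. A reader might infer from 14 and 20 that the sponsor expects to lose 30%, but no rate is stated. A reader might also infer that power falls from 79% to 61%, which is what a two-sided paired t-test at d = 0.65 gives with 20 and with 14 participants. The plan does not name that test, and by its own calculation 14 participants give 80%. That gap belongs to the separate question of how the sample size was calculated. The dropout allowance also covers refusals, which no change to this rule would recover.

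Third, withdrawal that depends on treatment is possible but not shown. The trial is blinded, each period is short and both sequences receive both treatments. The selection bias is therefore a risk of unknown size and direction.

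**Conclusion.** The conflict between *Dropout criteria* and *Data analysis* is real and lies in what the article states, not in what it leaves out. Followed as written, the rule stops outcome collection after non-adherence. Under the Friedman test or a standard repeated-measures 2 × 4 ANOVA, the analysis would in effect rest mainly on completers.

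The missed-session trigger alone would withdraw about 10% to 40% of participants, or roughly 2 to 8 of 20. This rests on assumed, independent miss rates of 1% to 5% per session. The conclusion also assumes that assessments end at withdrawal, which is the natural reading but is not spelled out. No figure can be put on the bias.

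**What to change.** Reconcile the two sections by separating stopping treatment from leaving the study.

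- Record a missed session or a change of rehabilitation as a protocol deviation, with its date and reason.
- Still carry out the remaining scheduled assessments where the participant consents.
- Analyse all randomised participants in their allocated sequence, using all available periods. A mixed model with treatment and period effects and a participant random effect is one suitable choice. It does not require all four assessments, although it assumes that what remains missing is explained by the observed data. Report by sequence how many have no post-intervention score.
- Use the present adherence rule only to define a per-protocol sensitivity set.

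Whether stimulation continues after a missed session or a change of rehabilitation remains a clinical decision, and this change does not touch it.

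The cost is a short amendment and a few assessments, already in the schedule, that are kept after non-adherence. The estimate may be somewhat diluted by partial adherence, and the per-protocol set would help to show how much.

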### Randomization

Participants will be randomly allocated to either group 1 (rTMS-active) or group 2 (rTMS-sham) with a 1:1 allocation defined by a computer-generated randomization using the R package (R Foundation for Statistical Computing) [32]. Randomization will be under the control of a blinded investigator who will be the only person allowed to manage the electronic security file of the randomization to assign the individuals. The investigator will be blind to the group in which the participant is allocated to.

### Blinding

The participants, researchers, and outcome assessors will remain blind to group allocation during the study. To ensure proper blinding, participants will receive codes and will be concealed from the allocation process by one different researcher. The researchers responsible for applying the intervention and the outcome assessors will not know the study design, allocation, objectives, and expected outcomes.

In addition, for the blinding of the experimenter (responsible for applying the intervention), one assessor (responsible for randomization) will be in charge of giving the active or sham coil to the experimenter. The sham coil has exactly the same shape of the active coil. Further details are presented in the “rTMS-sham” section.

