### Allocation concealment

Allocation concealment will successfully be reached since no one involved in this study (i.e. the participants, researchers, and outcome assessors) will be aware of the treatment allocations. Furthermore, investigators will have no control over the order of patients randomized. A blinded investigator will encode the individuals and groups of intervention. To perform the allocation procedure, the encoded groups will be placed inside a closed opaque envelope, which will be labeled with the code for each participant. Envelopes will be opened only during the time of active or sham intervention.

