### Primary outcomes

To evaluate the motor and sensory effects of the high-frequency rTMS in the lower-limb motor area on M1 (i.e. vertex, Cz) and check the possibility of generating motor gains in participants with iSCI, we will observe the change from baseline motor values provided by the ASIA score.

Only one researcher will be responsible for evaluating all of the participants through both the sensorimotor scales and electromyography (EMG). This researcher will be a physiotherapist who will also receive training to use the scales and EMG device. In addition, we will perform an evaluation of the intra-rater reliability of the instruments used in this study. Adverse events will be collected using a form for adverse events at each assessment point and any adverse event related to the intervention will be reported.

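### The protocol article declares the person who controls randomisation blind and says nobody knows the allocation, yet has the person responsible for randomisation hand out the active or sham coil

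*Protocol article*

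**What the plan says.** Four sections of the protocol article bear on who knows the treatment.

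- **Randomization:** one investigator, described as blinded, has sole charge of the computer file that holds the assignments, and nobody else may handle it. Of this person the section writes: "The investigator will be blind to the group in which the participant is allocated to".
- **Blinding:** the general claim covers three groups: "The participants, researchers, and outcome assessors will remain blind to group allocation during the study". Those who stimulate and those who rate are also to be kept unaware of how the trial is designed and of what it aims to show. The section then sets out how the operator is protected from learning the treatment, and gives a further person this task: "one assessor (responsible for randomization) will be in charge of giving the active or sham coil to the experimenter".
- **Allocation concealment:** whoever encodes participants and groups is again called blinded. The sealed envelopes are opened when each intervention is given, by someone not named. The overall claim made here is that "no one involved in this study (i.e. the participants, researchers, and outcome assessors) will be aware of the treatment allocations".
- **Primary outcomes:** the clinical scales and the muscle recordings alike fall to a single physiotherapist. The article words this as follows: "Only one researcher will be responsible for evaluating all of the participants".

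A different section, Intervention, bears on what operators can be expected to know about the trial. Its sentence on training reads: "The researchers will be trained to perform both rTMS-sham and rTMS-active interventions".

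**The concern.** A sham-device trial needs at least one person who can match each participant to the correct device. That person is normally unblinded and kept away from everything else. Here the article gives the task to the person in charge of randomisation, and elsewhere declares that person blind.

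Two things are at stake. The first is the accuracy of the blinding claim. The Background criticises earlier studies for being only single-blinded, and the Discussion presents this trial as the first fully randomised double-blind crossover trial in this population, so the description of blinding carries part of the case for the trial. The second is protection of the primary outcome. The ASIA motor score is a manual strength grade from 0 to 5 for each key muscle, given by one rater, and such a grade is open to expectation. Every participant receives both treatments, so anyone who learns the coil used in one period also knows the other. The separation between coil-giver and rater should therefore be plain, and the wording blurs it.

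**Working it through.** No arithmetic applies. The check sets the role statements side by side.

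**Step 1: who gives out the coil?** The Randomization section allows only one person to manage the allocation file. The Blinding section gives the coil hand-over to the assessor who is responsible for randomisation. The natural reading is that these are the same person. If they were two people, the second would still need information from a file that only the first may handle, so the difficulty would move but not disappear.

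**Step 2: can that person be blind?** To give the right coil, the dispenser must be able to get from participant to coil type. There are two ways.

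- *The dispenser knows which coil is active.* Then the dispenser is unblinded, and the sentence in Randomization is wrong.
- *The coils carry neutral codes and the dispenser sees only the code.* The article does not describe this. The Blinding and rTMS-sham sections mention matching shape, similar sound and contact with the skull. Allocation concealment mentions codes for participants and groups only. Even with coded coils, a sole manager of the file who can link group to code could decode the treatment.

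**Step 3: can it be true that no one knows?** Under either arrangement somebody must hold the key. The article calls the file manager blind and the encoder blind, and its general statement leaves nobody else. As written, no one could match a participant to the correct coil, so the statement in Allocation concealment fails whichever way Step 2 is resolved.

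**Step 4: what is left intact?** The claim in Blinding covers participants, researchers (including operators) and outcome assessors. A dispenser who knows the allocation is compatible with blind participants, a blind operator and a blind rater. The condition is that the dispenser takes none of those roles. For the rater, the article states that outcome assessors will not know the allocation, which points to separation. But it uses the word assessor for the dispenser too, and Primary outcomes has a single rater for all participants, so the condition is not clearly stated.

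**Step 5: what do operators know?** Blinding says that operators will not know the study design. Intervention says that the researchers are trained in both sham and active stimulation. Operators trained in both, who are then handed a coil by a third party, know at least that the trial is sham-controlled. This does not tell them the sequence or any participant's allocation. Only the claim about the design is too strong.

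**The case against.** **The blinding that matters is untouched.** In a sham-device trial the groups that count are participants, operators and outcome raters, and the article says that all three stay blind. The coil hand-over exists to keep the operator blind. This stands in full. A reader might infer that the double-blind status of the trial collapses; the documents do not support that.

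**The rater is a different person.** The Blinding section speaks of outcome assessors, who do not know the allocation, and separately of one assessor with a randomisation task. Primary outcomes gives the rater no randomisation or coil role. A reader might infer from the shared word that the sole rater is unblinded; the text gives no ground for that and points the other way. What remains is that the label is ambiguous, on a point where the trial depends on one person's grades.

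**The sentences can be read more narrowly.** The statement in Allocation concealment carries a list in brackets, and concealment concerns knowledge before assignment. The investigator might be blind only until the envelope is opened. This softens the conflict but does not remove it: the sentence in Randomization has no time limit, and after the first period's coil is handed over the whole sequence is known to whoever can identify it.

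**A journal article condenses role details.** It does, and missing detail on role separation would be no finding. The point rests on statements that the article makes and that conflict with each other.

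**The consequence could be expressed as a false-positive rate.** A reader might want to do so by supposing some amount of rating drift. The document gives no drift size, and the exercise would apply only if rater and coil-giver were the same person, which nothing shows.

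**Conclusion.** The concern holds as a contradiction about one role. The article says that the person controlling randomisation is blind and that nobody involved knows the allocations, and it describes a procedure in which the person responsible for randomisation must know the treatment or be able to decode it. That is wrong as written: a stated blinding property that the procedure does not provide.

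The conclusion rests on two readings: that the sole manager of the file and the person responsible for randomisation are the same, and that the coils are not coded, since no coding is described. If either reading is mistaken, the statement that no one knows still fails, because someone must hold the key.

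The size is limited. If the coil-giver has no other role, the harm is an inaccurate blinding statement, and the blinding of participants, operators and outcome assessors can stand. It is worth correcting because the primary outcome is a manual grade by one rater and the repair is cheap. The claim that operators are unaware of the design is a lesser overstatement.

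**What to change.** 1. Name one existing team member as the unblinded holder of the allocation code and the coils, and do not use the title assessor for this role.
2. State that this person does not apply stimulation, rate outcomes or analyse data, and is not the physiotherapist described under Primary outcomes.
3. In Randomization, replace the statement that the investigator is blind with one that fits the role. In Allocation concealment, replace the statement that nobody is aware with one that excepts the named holder.
4. In Blinding, soften the claim that operators do not know the study design, so that it agrees with the training described under Intervention. It is enough to say that they do not know any participant's allocation.
5. Keep the claim that participants, operators and outcome assessors are blind to allocation.

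This needs no additional participants, visits or procedures. The cost is a role assignment within the team and a short wording amendment, with a blinding statement that is slightly less sweeping but accurate.
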